## Abstract

**Introduction::**

Prostate-specific antigen (PSA) is the main tool for early detection, risk stratification and monitoring of prostate cancer (PCa). However, there are controversies about the use of PSA as a population screening test because of the high potential for overdiagnosis and overtreatment associated. The net benefit of screening is unclear and according to the available recommendations, it should be offered to well-informed men with an adequate health status and a life-expectancy of at least 10 years or to men at elevated risk of having PCa. In addition, the factors that influence test results are unclear, as is impact of false positive or negative results on patient health.

Our objective is to assess the clinical and analytical factors associated with the presence of false positive and false negative results and the diagnostic/therapeutic process followed by these patients.

**Methods and analysis::**

A prospective observational cohort study will be carried out. We will include a cohort of patients with a positive PSA result (1.081 patients) and a sample of patients with negative results (572 patients); both will be followed for 2 years by reviewing medical records to assess the variables associated with these results, as well as characteristics of patient management after a positive PSA value. We will include those patients with a PSA determination from 2 hospitals in the Valencian Community. Patients who have been previously diagnosed with prostate cancer or who are being followed for previous high PSA values will be excluded.

**Discussion::**

The study will estimate the frequency of false positive and false negative PSA results in routine clinical practice, and allow us to quantify the potential harm caused.

**Study registration::**

Clinicaltrials.gov (https://clinicaltrials.gov/): NCT03978299, June 7, 2019.

## Introduction

1

The number of cases of prostate cancer (PCa) has increased globally by 40% in 10 years, from 1.4 million in 2016 to 1.0 million in 2006.^[1]^ This increase has been associated with the introduction of Prostate Specific Antigen (PSA) testing in the 1990s, with the variation observed between countries explained by differences in use of PSA tests.^[2–4]^

The usefulness of PCa screening with PSA test in reducing mortality has been questioned for years due to contradictory results of two prospective randomized trials.^[5]^ Methodological limitations were observed in one of the trials, where more than 90% of men in the control group were screened anyway.^[6]^ A posterior analysis of both trials concluded that the benefit of screening in terms of PCa mortality reduction was similar in both (around 30%).^[7]^ In addition, an increase in the absolute effect of screening on PCa mortality has been described with longer follow-up.^[8]^ A retrospective cohort study has suggested that PSA screening has benefit in both PCa specific and overall mortality.^[9]^ While, a systematic review published in 2018 concludes that PCa screening leads to a small reduction in disease-specific mortality over 10 years but has no effect on overall mortality.^[10]^

Although PSA determination may help in the early detection of PCa, it has some limitations. First, it is not a specific PCa biomarker, as it can be high in other circumstances (such as acute prostatitis, benign prostatic hyperplasia, after catheter manipulations, etc). Second, PSA concentration is a continuous parameter, meaning that there is no universally accepted threshold value for PCa diagnosis, although normal values <4 μg/L are often used. Finally, it cannot detect the aggressiveness of tumors and can lead to overdiagnosis,^[11]^ meaning some cancers diagnosed by early detection develop so slowly that they may never cause the patient problems. It has been estimated that between 20 and 50% of PCa are overdiagnosed.^[12–14]^

There is no controversy about the harm resulting from PSA screening, such as consequences of overdiagnosis.^[14,15]^ Diagnoses associated not only with wasted resources and side effects of treatment, but also with severe, stress-induced psychiatric and somatic consequences.^[15]^ Therefore, various strategies have been studied to reduce these harms. A study that has evaluated low-intensity screening to reduce overdetection continued to deliver greater detection of low-risk PCa, without reducing mortality linked to PCa.^[16]^ While, active surveillance (AS) is a proposed serial monitoring program to reduce PCa overtreatment due to screening and avoid immediate therapy for patients with low-risk PCa.^[17]^ PCa mortality results described in patients with AS have been similar to low-risk patients with initial definitive intervention.^[18]^

Finally, the main North American and European professional associations provide a series of recommendations regarding opportunistic screening to reduce overdiagnosis. The U.S. Preventive Services Task Force (USPSTF) updated its recommendations in 2017, in which it indicated that opportunistic screening may be useful among men aged between 55 and 69 years of age but the decision to perform this test should be made by each patient individually and jointly with the clinician, after the patient understands the benefits and risks of screening.^[19]^ The European Association of Urology (EAU)^[20]^ recommends the doctors offer an individualized early detection strategy to informed patients with good performance status and life expectancy of at least 10 to 15 years with high risk of PCa (men older than 50 years or 45 years if they are African American or have a family history of PCa).

Furthermore, several clinical or sociodemographic factors may influence PSA levels, how results interpreted, and hence false positives or negatives in a PSA test. Previous studies have evaluated variations of PSA levels according to demographic parameters such as age,^[21]^ although the clinical significance of these variations has not been evaluated in clinical practice. Regarding race, there are studies that showed variations in PSA level^[22]^ while others found no differences.^[23]^ Some studies suggest that clinical factors such as diabetes^[24]^ and obesity^[25]^ are associated with a lower likelihood of having a positive PSA test. Similarly, treatments like statins,^[26]^ metformin^[27]^ or treatment for benign prostatic hypertrophy^[28]^ can also affect PSA results. Many of these factors are highly prevalent in the target population for PCa screening.

To date, there are no studies evaluating the impact of these factors on a false positive or negative PSA result performed in general practice. The majority of studies have been carried out as part of clinical trials that evaluate the usefulness of PSA as a screening test, where the population is different from that with a PSA determination in routine clinical practice. Clinical trials tend to include healthier and younger patients and often represent a highly selected patient population.^[29]^ The impact of PSA determination on the patient's clinical management and evolution has not been evaluated either. This includes possible adverse effects related to the diagnostic process (biopsy, surgery and treatment), and the relationship between PSA determination and other factors that are considered when making the decision to request a biopsy such as patient comorbidity, Charlson index and PSA density, index or velocity.

## Objectives

2

### Primary objective

2.1

The primary aim of the current research project is to evaluate the outcomes of PSA determinations, in general practice in two health departments of the Valencian Community (Spain).

### Specific objectives

2.2

1.To analyze the clinical and analytical factors associated with the presence of false positive and false negative results in PSA determinations in patients undergoing opportunistic screening or with symptoms suggestive of disease.2.To evaluate the patient's clinical outcome, and any diagnostic and/or clinical and/or therapeutic interventions over a 2-year period after PSA testing. Furthermore, we will study whether this management is appropriate to the recommendations of the European Association of Urology.

## Methods and analysis

3

This study will be carried out and reported according to with the Strengthening the Reporting of Observational Studies in Epidemiology (STROBE) Statement.^[30]^

### Study design

3.1

This is a prospective observational cohort study of patients with a PSA determination for the early detection of PCa or in the presence of prostatic symptoms, in the general practice. The study protocol is registered at https://clinicaltrials.gov (ClinicalTrials.gov Identifier: NCT03978299).

### Study population

3.2

#### Eligibility criteria

3.2.1

Participants will be a random sample of men from the Health Departments 17 and 19, in the Valencian Community (these include 20 primary health centers and 2 hospitals: General University Hospital of Sant Joan d’Alacant and General University Hospital of Alicante, respectively). These are referral hospitals for all individuals living in their catchment areas and belong to the National Health Care System (the majority of the population in Spain uses the National Health System (NHS) as the main medical service (the publicly funded insurance scheme covers 98.5% of the Spanish population). We will include men over 18 with a PSA determination requested in a routine health examination from January to April 2018. Patients who do not belong to the NHS or have been previously diagnosed with PCa or who are being followed for previous high PSA values will be excluded.

We will select a cohort of patients with positive PSA results (defined as total PSA value is >10 μg/L or a total PSA between 4 and 10 μg/L if the value of the free PSA/total PSA fraction is <25% in at least in two determinations) and a cohort of patients with negative results (defined as total PSA value is < 4 μg/L or a total PSA between 4 and 10 μg/L if the value of the free PSA/total PSA fraction is >25%) among subject included in a previous cross-sectional study (NCT03968692) that we are carrying out (registered in ClinicalTrials.gov (NCT03968692)). This cross-sectional study aims to describe the PSA determinations that are performed in clinical practice and their appropriateness according to the available recommendations, considering sociodemographic and clinical characteristics of the patients.

#### Sample size and recruitment procedure

3.2.2

According to a review by the American Cancer Society,^[31]^ a value of PSA of 4 μg/L had an estimated sensitivity of 21% to detect any type of prostate cancer and a specificity of 91%. We estimate a prevalence of PCa in this population not lower than 5% (given that we include asymptomatic and symptomatic patients), with a 95% margin of error and 2% precision, we will need to include 457 patients with a negative PSA result and 865 PSA-positive patients. Taking into account a 20% possible loss during follow-up, we will increase to 572 patients with a negative PSA result (286 per center) and 1081 patients with a positive PSA result (541 per center) who will be selected consecutively from among those included in the previous cross-sectional study (NCT03968692) until we reach the proposed sample size. We will use the initial randomized list (which included determinations during the first 4 months of 2018) to select patients who meet both negative and positive PSA criteria and if it is necessary, we will continue to review analyses until the sample size is achieved. (Fig. 1)

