### Statistical analysis

3.5

The analysis will be performed using the Stata IC 15 program.

-Specific objective 1. We will calculate the proportion of false positive and false negative results for the diagnosis of PCa and the associated variables. In the case of false positive tests, we will also describe the time from a positive PSA result until PCa is ruled out using mean, standard deviation or median and interquartile ranges for the total population and relevant subgroups. In order to analyze clinical and analytical factors associated with the presence of false positive and false negative results in PSA determinations, we will calculate prevalence ratios and their 95% confidence interval with log-binomial regression.-Specific objective 2. We will assess the probability of having a diagnostic, surgical or therapeutic intervention according to variables using risk ratios with their 95% confidence intervals. If necessary, we will adjust for potential confounders using log-binomial regression. We will also evaluate the agreement between the interventions performed and the available guidelines.^[20]^ We will evaluate the inter-observer agreement in the determination of appropriateness using the Kappa index.

Steps will be taken to prevent missing data (e.g., we will periodically review medical records and access data from different sources such as records of primary, specialized and hospital care), but some level is unavoidable and we will incorporate methods analyzing missing data or data from uncertain sources when necessary.^[33,34]^

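### The 2% precision in section 3.2.2 is stated without condition, but it rests on a minimum prevalence, which is the favourable end for an absolute half-width

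*Protocol article*

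**What the plan says.** Section 3.2.2 (Sample size and recruitment procedure) of the protocol article takes from a published review that "a value of PSA of 4 μg/L had an estimated sensitivity of 21% to detect any type of prostate cancer and a specificity of 91" percent. It continues: "We estimate a prevalence of PCa in this population not lower than 5% (given that we include asymptomatic and symptomatic patients"), and "with a 95% margin of error and 2% precision", "we will need to include 457 patients with a negative PSA result and 865 PSA-positive patients". I read the 95% as the confidence level and the 2% as an absolute half-width in percentage points.

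For losses ("Taking into account a 20% possible loss during follow-up") the cohorts become 572 negatives and 1081 positives. The section gives no likely or upper prevalence and no precision at any other value.

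Section 3.5 (Statistical analysis) shows what the precision is for: "We will calculate the proportion of false positive and false negative results for the diagnosis of PCa and the associated variables". The cohorts are selected on the PSA result (section 3.2.1). Each can therefore directly estimate a fraction conditional on that result: the cancer fraction among positives, whose complement is the false-positive fraction, and the cancer fraction among negatives.

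**The concern.** A minimum is a safe planning value only if the requirement eases as the quantity rises. For an absolute half-width the reverse holds below 50%. The variance p(1−p) grows with p, so a prevalence above the floor makes the interval wider. The reason given for the floor, that symptomatic men are included, also points upward.

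The 2% is the only performance figure given for the size of the study, and the Abstract and Discussion promise the frequencies of false-positive and false-negative results. A reader would take ±2 points as what the study is expected to achieve, when it is close to the best that the stated inputs allow.

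**Working it through.** **Inputs, all from section 3.2.2:** prevalence at least 5%; sensitivity 21%; specificity 91%; 95% confidence; half-width d = 0.02; 457 negatives and 865 positives evaluable; 20% loss.

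**Formulas.** Required number n = 1.96² · q(1−q) / d². Half-width = 1.96 · √(q(1−q)/n). Here q is the cancer fraction in the cohort; the false-positive fraction 1−q has the same half-width.

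**Reproducing the plan's figures**
- Negatives, q = 5%: 1.96² × 0.05 × 0.95 / 0.0004 = 456.2, so 457. Exact match.
- Positives, q = 10%: 1.96² × 0.10 × 0.90 / 0.0004 = 864.3, so 865. Exact match, but 10% is not stated. Neither q = 5% (457) nor q = 9%, one minus specificity (787), gives 865.
- Losses: 457/0.8 = 571.25, so 572; 865/0.8 = 1081.25, given as 1081. The rounding is immaterial.

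**What the quoted inputs imply at the floor**
- Positives: 0.21 × 0.05 / (0.21 × 0.05 + 0.09 × 0.95) = 0.0105/0.0960 = 10.9%. With 865 men the half-width is ±2.08 points; ±2 needs 936.
- Negatives: 0.79 × 0.05 / (0.79 × 0.05 + 0.91 × 0.95) = 0.0395/0.9040 = 4.4%. With 457 men the half-width is ±1.87 points.

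**Above the floor.** The prevalences of 10%, 15% and 20% are my assumptions. The table also assumes that 21% and 91% apply and that every cancer is found.

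| Prevalence | Cancer fraction, positives | Half-width, 865 | n for ±2 | Cancer fraction, negatives | Half-width, 457 | n for ±2 |
|---|---|---|---|---|---|---|
| 5% | 10.9% | ±2.08 | 936 | 4.4% | ±1.87 | 402 |
| 10% | 20.6% | ±2.69 | 1571 | 8.8% | ±2.60 | 771 |
| 15% | 29.2% | ±3.03 | 1985 | 13.3% | ±3.11 | 1107 |
| 20% | 36.8% | ±3.21 | 2235 | 17.8% | ±3.51 | 1408 |

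Both fractions stay at or below 50% up to 30% prevalence, where the positives reach exactly 50%, so the half-widths widen throughout that range.

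**Limits for ±2 points.** In terms of prevalence, 865 positives hold ±2 up to about 4.5% and 457 negatives up to about 5.7%. If nobody were lost (1081 and 572), the limits would be about 6.0% and 7.3%, and at 10% prevalence the half-widths would be ±2.41 and ±2.32. The loss allowance shifts the limits but does not remove the dependence.

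**The case against.** A reader might infer that both cohorts were sized at 5%. The document does not support that: only 457 reproduces from 5%, and 865 reproduces from 10%. Nor does it show that 865 is a miscalculation. The 10% may be a rounded 10.9% or may be explained in the full protocol, which a journal article can leave out.

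A reader might also infer that the design fails to deliver its 2%. That is too strong. At 5% prevalence the half-widths are ±2.08 and ±1.87, which is ±2 for practical purposes. The article gives no upper prevalence, so every row above 5% is an assumption.

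The strongest objection is that the table may not describe what the study will observe. A false negative counts only if cancer is diagnosed within two years (section 3.4), and negatives are followed by annual record review (section 3.3). If, as an illustration, half of the cancers surface at 10% prevalence, the observed fraction is about 4.4% and the half-width 1.96 × √(0.044 × 0.956/457) = ±1.9 points, inside 2%. At 20% prevalence the same halving gives about 8.9% and ±2.6. Among positives, a negative rectal examination and/or biopsy can settle a false positive (section 3.4), so the observed cancer fraction may again fall below the calculated one. Positivity is also a composite of total PSA and the free fraction in repeat determinations (section 3.2.1), whereas 21% and 91% belong to a 4 μg/L cut-off. All of this stands and means the table cannot be offered as the precision the study will achieve.

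Finally, 5% is the favourable end only on the absolute scale. For negatives, relative precision improves with prevalence: ±1.87 on 4.4% is about 43%, ±2.60 on 8.8% about 30%. The listed objective 1 outcomes are associations, and for false negatives more events help those. This limits the consequence, but the plan states its precision on the absolute scale and will report the proportions.

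**Conclusion.** The point holds in a limited form. The plan gives prevalence as a minimum and then states 2% precision without condition, although a minimum below 50% is the favourable end for an absolute half-width. The figure holds for negatives only while their cancer fraction is 5% or lower. For positives it holds only while theirs is 10% or lower, and the plan's own inputs put that fraction at 10.9% even at the floor.

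At the floor the discrepancy is about 0.1 point. At assumed prevalences of 10% to 20% the half-widths are 2.6 to 3.5 points, roughly 30% to 75% wider than stated (2.60/2 = 1.30; 3.51/2 = 1.76). That size rests on the quoted sensitivity and specificity, full ascertainment and prevalences the document does not give. The direction does not depend on the particular prevalences: if the observed cancer fraction rises above the planning value, the interval widens. This is an over-favourable statement of precision and does not require more patients.

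**What to change.** Keep the cohort sizes. In section 3.2.2:

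1. Name the planning proportion for each cohort: 5% for negatives and, if the sponsor confirms it, 10% for positives.
2. Replace the unconditional 2% with expected 95% half-widths (positives / negatives) over assumed prevalences: about ±2.1 / ±1.9 points at 5%, ±2.7 / ±2.6 at 10% and ±3.2 / ±3.5 at 20%. Label these as assumptions resting on the quoted 21% and 91% and on full ascertainment.
3. State that about ±2 points is the favourable end for absolute precision, and that half-widths for the negatives will be smaller if only part of the cancers are diagnosed within two years.

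The cost is a sentence or two and a less favourable precision statement. There are no extra patients and no change to design or analysis.

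### The 2% precision claim rests on a PPV cut from 10.94% to 10% and on the lowest prevalence the plan allows, so it is narrowly missed for PSA-positives at 5% and not assured in either cohort above it

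*Protocol article*

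**What the plan says.** Section 3.2.2 takes from a published review "an estimated sensitivity of 21% to detect any type of prostate cancer and a specificity of 91" percent, for a PSA cut-off of 4 μg/L. It adds "We estimate a prevalence of PCa in this population not lower than 5" percent, and justifies this by the inclusion of symptomatic as well as asymptomatic men. It then sets a 95% level and concludes: "2% precision, we will need to include 457 patients with a negative PSA result and 865 PSA-positive patients". Both numbers are raised on this basis: "Taking into account a 20% possible loss during follow-up". The recruitment targets become 572 negatives and 1081 positives.

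Section 3.2.1 (Eligibility criteria) selects the two cohorts on the PSA result. Its positive rule is more than a single cut-off at 4 μg/L: between 4 and 10 μg/L it also requires "free PSA/total PSA fraction is <25% in at least in two determinations". Section 3.5 (Statistical analysis) plans to estimate the proportions of false positive and false negative results.

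**The concern.** In cohorts chosen by test result, the estimable proportions are 1 − PPV among positives and 1 − NPV among negatives. Sample sizes built on the stated accuracy and prevalence should therefore match those quantities. On a first check they do not: 457 is the number for a proportion of 5% and 865 the number for 10%, and 10% appears nowhere in the section.

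The prevalence is also given as a lower bound. A lower bound is a safe planning value only if the requirement falls as prevalence rises, and here it rises. The plan itself gives a reason to expect more than 5%, because symptomatic men are included. The 2% is the only precision the protocol promises, so readers would take it as a property of the design.

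**Working it through.** **Inputs (section 3.2.2).** Sensitivity 0.21, specificity 0.91, prevalence 0.05, half-width d = 0.02. The stated 95% is read as two-sided confidence, z = 1.96.

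**Predictive values at 5% prevalence.**
- PPV = (0.21 × 0.05) / (0.21 × 0.05 + 0.09 × 0.95) = 0.0105 / 0.0960 = 10.94%
- NPV = (0.91 × 0.95) / (0.91 × 0.95 + 0.79 × 0.05) = 0.8645 / 0.9040 = 95.63%, so 1 − NPV = 4.37%

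**Reproducing the plan's figures.** With n = z²p(1 − p)/d² = 3.8416 × p(1 − p)/0.0004:
- NPV cut to 95%: 3.8416 × 0.95 × 0.05/0.0004 = 456.2, so 457
- PPV cut to 10%: 3.8416 × 0.10 × 0.90/0.0004 = 864.4, so 865

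Both stated numbers come back exactly from one rule, dropping the decimals. The inflation for loss also follows: 457/0.8 = 571.25 and 865/0.8 = 1081.25.

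**Without the cut.**
- Positives: 3.8416 × 0.1094 × 0.8906/0.0004 ≈ 935.5, so 936 are needed. With 865 the half-width is 1.96 × √(0.1094 × 0.8906/865) = 2.08 points.
- Negatives: 3.8416 × 0.0437 × 0.9563/0.0004 ≈ 401.3, so 402 are needed. With 457 the half-width is 1.96 × √(0.0437 × 0.9563/457) = 1.87 points.

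**Effect of prevalence.** Sensitivity and specificity are held at 21% and 91%. Prevalences above 5% are illustrative assumptions; the document gives none.

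| Prevalence | PPV | 1 − NPV | n for 2 points (pos / neg) | Half-width, 865 / 457 evaluable | Half-width, 1081 / 572 (no loss) |
|---|---|---|---|---|---|
| 5% | 10.94% | 4.37% | 936 / 402 | 2.08 / 1.87 | 1.86 / 1.68 |
| 10% | 20.59% | 8.80% | 1571 / 771 | 2.69 / 2.60 | 2.41 / 2.32 |
| 15% | 29.17% | 13.28% | 1985 / 1107 | 3.03 / 3.11 | 2.71 / 2.78 |
| 20% | 36.84% | 17.83% | 2235 / 1408 | 3.21 / 3.51 | 2.88 / 3.14 |

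PPV and 1 − NPV both rise with prevalence and stay at or below 50% up to a prevalence of 30%, so p(1 − p), and with it the required n, rises throughout that range. A PPV of 10% would need a prevalence of 4.55%, below the plan's own floor. For negatives, 1 − NPV reaches 5% at a prevalence of about 5.7%, and 457 keeps 2 points only up to there.

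**The case against.** Four points can be made for the plan.

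First, a reader might infer that 457 and 865 have no link to the stated inputs, with prevalence mistaken for the proportion and a foreign 10% brought in. The document does not support that. Truncated PPV and NPV return both numbers exactly, which is the most economical explanation. What stands is a rounding error in PPV, not an unexplained derivation. Leaving the formula unstated is ordinary condensation in an article and is not held against it.

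Second, at exactly 5% prevalence little is lost. The positives miss by 0.08 points, and 2.08 rounds to 2; the negatives do better than promised. If loss among the 1081 recruited stays below about 13% (936/1081 = 86.6%), the positives also meet the target at 5%. This is right, and it rules out saying that 2% fails in both cohorts at the stated inputs.

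Third, the larger half-widths depend on prevalences that the document never gives. That is also right, so their size is illustrative. The direction is not: the plan commits only to a floor, and required numbers rise above it.

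Fourth, a reader might infer that the study's stricter positive rule must raise specificity, hence PPV, and so widen the interval. That holds only if sensitivity stays at 21%, whereas a stricter rule would also tend to lower sensitivity. For example, by assumption, sensitivity 14% and specificity 94% at 5% prevalence give PPV = 0.0070/0.0640 = 10.9%, essentially unchanged. All that can be said is that the inputs describe another rule and that PPV and NPV may differ in either direction.

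**Conclusion.** Wrong as written, of minor to moderate severity. At the stated inputs the error is small: PPV was apparently cut from 10.94% to 10%, leaving the positive cohort 71 evaluable patients short of 936 and its half-width at 2.08 points. The negative cohort meets the target.

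The more important fault is that an unqualified 2% is attached to a prevalence floor. With the planned evaluable numbers, the positives miss 2 points at the floor and above it, and the negatives miss it above about 5.7%. At an assumed prevalence of 10% the half-widths are about 2.7 and 2.6 points, and at 20% about 3.2 and 3.5. Even with no loss to follow-up, neither cohort reaches 2 points at 10%.

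These figures rest on the normal-approximation formula, on 21% and 91% holding for the study's rule, and on PPV and NPV being the parameters that were sized, which is an inference. The final confidence intervals will show the precision achieved, so no planned analysis is invalidated; the fault lies in what the design claims.

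**What to change.** Keep enrolment as planned and rewrite the sample size paragraph in section 3.2.2:

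- Name PPV and NPV (equivalently, the false positive and false negative proportions within each cohort) as the parameters sized, with the formula.
- Give their values at 5% prevalence as 10.94% and 95.63%, correcting the PPV rounding.
- Replace the unqualified 2% with the expected half-widths for 865 and 457 evaluable patients: 2.1 and 1.9 points at 5% prevalence, and the corresponding values over a range of higher prevalences that the investigators state and justify.
- Note that 21% and 91% refer to a single 4 μg/L cut-off, while the rule in section 3.2.1 adds the free/total fraction and repeat determinations, so PPV and NPV may differ in either direction.

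The cost is one paragraph and a somewhat less favourable precision statement. No extra patients and no change to the analysis are needed.

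### The 865 PSA-positive men do not follow from the stated inputs: the implied PPV of 10.94% needs 936, and ±2 points is a best case because 5% prevalence is a minimum (minor)

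*Protocol article*

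**What the plan says.** Section 3.2.2 (Sample size and recruitment procedure) prints both the inputs and the result.

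- Test performance at a PSA of 4 μg/L: "estimated sensitivity of 21% to detect any type of prostate cancer and a specificity of 91"%.
- Prevalence: "We estimate a prevalence of PCa in this population not lower than 5"%.
- Confidence and precision: "with a 95% margin of error and 2% precision". I read this as a 95% confidence interval with a half-width of 2 percentage points.
- Result: "we will need to include 457 patients with a negative PSA result and 865 PSA-positive patients".
- Inflation: "Taking into account a 20% possible loss during follow-up", the numbers become 572 negative and 1,081 positive.

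No formula is given, and no expected proportion for either cohort. Section 3.5 (Statistical analysis) gives the quantities to be estimated under specific objective 1: "We will calculate the proportion of false positive and false negative results for the diagnosis of PCa and the associated variables".

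**The concern.** The positive cohort is selected on a positive test, and its main descriptive result is the share of those men whose result was false. Sensitivity, specificity and prevalence combine to give exactly that share (1 − PPV). They give the matching share for the negative cohort too (1 − NPV, where NPV is the negative predictive value). Putting the stated values into the usual precision formula should therefore return 865, and it does not.

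If 865 is too small for its own inputs, the claimed precision of the false-positive proportion is not what the plan delivers. A second issue is that prevalence enters as a lower limit but is used as a point value. In both cohorts the required number rises as prevalence rises over the range checked below, so a calculation at the floor gives the most favourable precision within the plan's own assumption.

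**Working it through.** **Inputs (all from section 3.2.2).** Sensitivity 0.21, specificity 0.91, prevalence 0.05 as the minimum, z = 1.96, half-width d = 0.02, loss 20%.

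**Formula.** n = z² p(1 − p)/d², rounded up. Using p or 1 − p gives the same n.

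**Reproducing the stated numbers**
- p = 0.10: 3.8416 × 0.0900/0.0004 = 864.4, so 865.
- p = 0.05: 3.8416 × 0.0475/0.0004 = 456.2, so 457.
- Loss: 457/0.8 = 571.25, so 572. 865/0.8 = 1,081.25, stated as 1,081. The inflation step is consistent.

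The formula is therefore almost certainly the one used, with p = 10% for the positives and p = 5% for the negatives. The 10% is not among the stated inputs. Other stated or derived proportions put into the same formula do not give 865:
- 1 − specificity (9%) gives 787.
- The test-positive fraction (9.6%) gives 834.
- Sensitivity (21%) gives 1,594.

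**What the inputs imply at 5% prevalence**
- PPV = 0.21 × 0.05/(0.21 × 0.05 + 0.09 × 0.95) = 0.0105/0.0960 = 0.1094.
- n for positives = 935.5, so 936. This is 71 more than 865. After 20% loss, 936/0.8 = 1,170, against 1,081.
- Half-width with 865 men: 1.96 × √(0.1094 × 0.8906/865) = 2.08 points.
- 1 − NPV = 0.79 × 0.05/(0.79 × 0.05 + 0.91 × 0.95) = 0.0395/0.9040 = 0.0437.
- n for negatives = 401.3, so 402.
- Half-width with 457 men: 1.96 × √(0.0437 × 0.9563/457) = 1.87 points.

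**Above the floor.** The same formulas, with half-widths at the 865 and 457 men left after 20% loss. The 6% and 10% prevalences are illustrations; the protocol gives no upper value.

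| Prevalence | PPV | n needed | Half-width, positives | 1 − NPV | n needed | Half-width, negatives |
|---|---|---|---|---|---|---|
| 5% | 10.94% | 936 | ±2.08 | 4.37% | 402 | ±1.87 |
| 6% | 12.96% | 1,084 | ±2.24 | 5.25% | 478 | ±2.04 |
| 10% | 20.59% | 1,571 | ±2.69 | 8.80% | 771 | ±2.60 |

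**Where each number stops being enough**
- Positives: 865 suffices while PPV is at most 10%. Solving 0.21q × 0.9 = 0.1 × 0.09(1 − q) gives q = 0.009/0.198 = 4.5%, below the stated floor.
- Negatives: 457 suffices while 1 − NPV is at most 5%. Solving 0.79q × 0.95 = 0.05 × 0.91(1 − q) gives q = 0.0455/0.796 = 5.7%.

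**The case against.** **The target is inferred.** The text names neither PPV nor 1 − PPV. That is true, and 936 depends on it. Still, it is the natural use of sensitivity and specificity for a cohort chosen on a positive test, and the other proportions checked do not return 865.

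**The gap is trivial.** At 5% prevalence the half-width is 2.08 points, which rounds to 2. If all 1,081 men were followed it would be 1.86. Since 1 − 936/1,081 = 13.4%, ±2.00 is met whenever loss stays below about 13%. This stands, and it is why the point is minor. It does not remove the point: the plan allows for 20% loss and treats 5% as a minimum, so the 2% claim is optimistic for the positive cohort at every prevalence it assumes once that loss occurs.

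**An article may omit working.** A missing formula or intermediate value alone would be no finding. Here the article prints inputs and a result that do not agree.

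**Two stronger readings a reader might infer.** The first is that 457 is also wrong. It is not: it meets ±2 points at 5% prevalence, and exceeding the required number is no error. The second is that the two cohorts were sized on different quantities, PPV for one and overall prevalence for the other. The article does not establish that. Rounding PPV (10.94%) and 1 − NPV (4.37%) to the nearest 5% gives 10% and 5%, which reproduces both 865 and 457. The text does not show which route was taken. Coarse rounding would not rescue 865 either, since 10.94% to the nearest whole per cent is 11%, which needs 941.

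**Conclusion.** The point holds, as a minor one. Taking PPV (or its complement) as the sizing target, the inputs in section 3.2.2 require 936 evaluable PSA-positive men; the stated 865 corresponds to an unstated 10%. After the planned loss the half-width at 5% prevalence is ±2.08 points rather than ±2.00. The negative cohort is adequate at the planning value. Because 5% is a floor, these are best-case figures for both cohorts; at 10% prevalence they become about ±2.7 and ±2.6 points.

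The results assume a single-proportion normal-approximation interval and that 21% and 91% apply to the study's test. The second assumption is only approximate: those figures are for the 4 μg/L cut-off, whereas section 3.2.1 also uses the free/total PSA fraction between 4 and 10 μg/L. The documents give no sensitivity or specificity for that combined rule. It would go too far to conclude that the study is seriously undersized: at 5% prevalence the loss of precision is under a tenth of a point.

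**What to change.** In section 3.2.2:

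1. Keep 1,081 and 572.
2. Name the proportion each cohort is sized on and its expected value. From the stated inputs at 5% prevalence these are PPV 10.94% and 1 − NPV 4.37%. If 10% was intended for the positives, state it and justify it.
3. Replace the flat 2% precision with half-widths after 20% loss: about ±2.1 points (positives) and ±1.9 (negatives) at 5% prevalence, widening to about ±2.7 and ±2.6 at 10%.
4. Add that the figures are approximate because the sensitivity and specificity refer to the 4 μg/L cut-off and not to the full definition in section 3.2.1.

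The cost is a few sentences. No extra patients are needed, and no analysis changes.
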